#### Training

Intervention groups will receive the usual ICS training about the functionality of the electronic health record system, with some changes. The usual training is provided for regional ECAP coordinators, who then train the health care teams in the region. For the purposes of the clinical trial, training will be provided only for teams allocated to intervention groups. The directors of each of these PCCs will be contacted before the training process begins.

One 2-h session will be provided for each of the three intervention groups during the first 3 weeks of the trial, to be attended by the regional ECAP coordinators and PCC directors, representing their teams. The research team will explain to each group how the reminder system works in that specific arm of the study. The PCC directors will then be responsible for training the rest of the professional team, independently and without supervision or follow-up by the research team, who will nonetheless be available to answer questions that may arise.

### Pilot study

Before the intervention begins, a 2-month pilot study will be conducted in two primary care teams under actual working conditions (patient situations and work setting). All professionals on these two teams will have access to all three reminder formats. In this phase, any problems will be addressed. At the end of the pilot study, an ad hoc survey will be administered to assess the participant’s’ response to the intervention, their level of satisfaction, and any additional suggestions for improving the reminder system. Throughout the intervention, the teams participating in the pilot test will continue to receive the reminders in the format of their choice but will be excluded from the analysis of the clinical trial outcomes.

### Outcomes

The main outcome variable is the health professional’s adherence to the reminder, measured as the proportion of patients receiving the recommended attention (yes/no) and the time elapsed between the first reminder message and implementation of the recommended action (months). Reminders will be considered “resolved” when the professional has completed the recommended actions (Table 2).

**Table 2 Tab2:** Reminders seen by the health professional, corresponding clinical condition, and the resolution

Reminder	Clinical condition	Resolution
Control blood pressure	Arterial hypertension/Elevated cardiovascular risk	Most recent blood pressure reading within 1 year shows ≤140/90 mmHg or 150/95 mmHg, depending on cardiovascular risk status
Control glycated hemoglobin	Type 2 diabetes mellitus	Most recent glycaemia test within 1 year shows HbA1c ≤ 8 %
Control cholesterol	Cerebrovascular accident/ischemic heart disease	Most recent cholesterol test within 1 year shows LDL ≤120 mg/dl
Screen for retinopathy	Type 2 diabetes mellitus	Record of thorough eye examination within past 2 years
Encourage smoking cessation	Smoking habit	Last record says “non-smoker”
Vaccinate for hepatitis B	Hepatitis C	Record of vaccination
Treat with ACEI	Heart failure	Active ACEI/ARB prescription
Treat with beta blockers	Heart failure/Ischemic heart disease	Active beta blockers prescription
Treat with antiplatelet or anticoagulant drugs	Atrial fibrillation	Active prescription for antiplatelet or anticoagulant drugs, as appropriate
Treat with antiplatelet drugs	Cerebrovascular accident/Ischemic heart disease	Active antiplatelet prescription

*Hb* haemoglobin, *LDL* low-density lipoprotein, *ACEI* angiotensin-converting enzyme inhibitor, *ARB* angiotensin receptor blocker, *HbA1c* glycated haemoglobin

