### Objectives

#### Primary objectives

To determine the effectiveness of reminders compared to no reminders in improving adherence to multiple clinical recommendations measured as the resolution of the clinical condition that motivated the reminder, in a primary care setting with a well-established feedback system.

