**Fig. 1 Fig1:**
[figure not shown]
Feedback screen that can be accessed by health professionals from the electronic health records system. Well-established feedback without reminders (control group)

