**Fig. 2 Fig2:**
[figure not shown]
Detail of the feedback screen to which health professionals have access. Well-established feedback without reminders (control group)

In contrast to the intervention with point-of-care reminders that will be evaluated using the present protocol, the usual monthly feedback screen (control group) does not allow direct interaction with the clinical health record system; this feedback is associated with the professional, not the individual patients, and requires that the health professional actively seek out the numerical results or the patient lists from which the established feedback screen draws the relevant data.

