Health professionals can also choose to view the reminders in their daily schedule of patients. The reminder provides a link to the patient’s electronic health record, from which the pertinent action can be taken (generate a prescription, record a vaccination, request a laboratory test, or record a clinical variable). There is also an option to ignore or exclude a recommendation for a particular patient and enter a comment about the reason for the exclusion.

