#### Intervention groups

The reminders can appear in the electronic health record screens in 3 levels. Each intervention group will receive a distinct, incremental presentation of the reminders: pop-up only, pop-up plus calendar icon, and pop-up plus calendar icon, with a customizable option.Pop-up windowHealth professionals allocated to this group will access a patient’s electronic health record; if a reminder has been generated for that patient, a pop-up window will present all of the patient reminders. No other display option will be available. The pop-up appears automatically to the professional on accessing the patient record from their calendar list of patients with an appointment. Before entering any other information they have to close the pop-up or click on the reminder to address the issue.Pop-up + calendar iconEach health professional has an online calendar with the list of patients scheduled for the day. The professionals allocated to this arm will be alerted to any reminders pertaining to each patient on the daily schedule. A square orange or red icon will appear next to the patient’s name, indicating the most important reminder (moderate or high) generated, with a small number showing the total number of reminders for that patient. This icon will be linked to the patient’s electronic health record with the pop-up window described for the first study arm.This level of intervention (in addition to just the pop-up window) gets a calendar icon. As for the pop-up, health professionals sees this window every time they access the patient’s record from the appointments calendar, the content of the pop-up being the unaddressed reminders, As for the calendar icon, the professionals see them every time they navigate to the calendar list of patients with an appointment.Configurability (pop-up + calendar icon + configuration options)The default configuration will show all reminders generated for a specific patient. Health professionals allocated to this group will be able to modify the default configuration, adding filters to select only the reminders they want to see integrated into the electronic health record. This option will be added to the pop-up window (which will still allow access to the expanded list of reminders) and the calendar alerts (which will continue to indicate the total number of reminders generated). Screenshots and detailed description of the intervention (Fig. 4).

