### Data collection and management

The ICS primary care information system (SISAP) will be used to identify patients with a health status that could be improved by the health reminders, and execute a weekly update of patient status. The variables required to execute these algorithms will be obtained from the clinical registry of electronic health records. They include patient diagnoses (by CIE-10 code), primary care visits, clinical variables, drug prescriptions, and vaccinations. In addition to the variables specific to the intervention (resolution of the reminder), other explanatory and descriptive variables will be collected (Table 3). Data for the EQR (quality of data recording) will be collected from the SIDIAP database (*Sistema d’Informació per al Desenvolupament de la Investigació en Atenció Primària*) (Bolíbar et al. 2012). Moreover, the Medea socioeconomic index (Domínguez-Berjón et al. 2008). The EQA, EQPF (prescription quality standard), and other variables at the level of the professional or PCC will be obtained from the ICS information system.

**Table 3 Tab3:** Variables included in multi-level analysis

Variable	Explanation
Variables at the reminder level	
Type of clinical activity required^a^	Preventive or follow-up activities, immunizations, treatment initiation
Reminder generated	Yes or no
Clinical situation can be improved	Described in Table 1
Age and sex^a^	Older populations generate a higher number of clinical situations that can be improved because of the relationship between age and morbidities
Comorbidity, weighted according to CRG^a^	CRG (Clinical related groups) classify patients according to morbidity, based on diagnoses, status and severity in different categories. Each category has a morbidity weight. A priori, greater morbidity should generate a greater number of improvable clinical situations
Variables at the professional/PCC level	
Socioeconomic level of the PCC	Medea Index
Rurality	Construct based on size of municipality and population/Km^2^
Teaches family medicine	PCC or team member is accredited for postbaccalaureate training in Family and Community Medicine
Teaches basic nursing	PCC or team member is accredited for baccalaureate training in Nursing

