### Time to resolution of the improvable clinical situation

Time to resolution will be estimated by the Kaplan–Meier method and comparisons will be done using the log-rank test. Multilevel survival analysis will be used to homogenize the data structure (Yau 2001). The analytical strategy is the same as described above: an initial model will be adjusted to estimate the intervention effect, introduce the professional-level variables (EQA, EQR, EQPF), and then determine whether the variables at the reminder level change the estimated intervention effect.

The level of significance will be established at 5 %. All analysis will be done using the Stata/SE software, version 11.2 (StataCorp 2012).

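### Time to resolution is counted from the first reminder message, an event that cannot occur in the control arm, so the between-arm time comparison has no valid time zero there

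*Protocol article*

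**What the plan says.** In the Outcomes section the main outcome variable has two parts: a yes/no proportion, and "the time elapsed between the first reminder message and implementation of the recommended action (months". The abstract uses the same definition, so it is not an isolated slip.

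The primary objective is "To determine the effectiveness of reminders compared to no reminders". The Fig. 1 legend describes the comparator as "Well-established feedback without reminders (control group". The text below the Fig. 2 legend adds that "this feedback is associated with the professional, not the individual patients", so the monthly feedback cannot stand in for a dated message about a given patient.

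For the reminder arms, the Intervention groups section says: "The pop-up appears automatically to the professional on accessing the patient record from their calendar list of patients with an appointment". Two of the three arms also have an icon on the daily appointment list.

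Under Data collection and management, the information system is to "identify patients with a health status that could be improved by the health reminders, and execute a weekly update of patient status". That sentence is not limited to any arm, but the flag date is not named as the start of follow-up.

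The time analysis is headed "Time to resolution of the improvable clinical situation". It plans Kaplan–Meier curves, log-rank tests and multilevel survival models, and gives no start date.

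**The concern.** A survival comparison between randomised arms needs a start date that exists in every arm and has the same meaning in each. Here the stated start is part of the intervention itself. Taken literally, control situations have no time zero, and the part of the research hypothesis about faster implementation cannot be tested.

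This is more than a detail left to an analysis plan. The article fixes the origin, and fixes it at an event that one arm cannot have, so a later plan would have to replace the definition rather than complete it.

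The practical risk lies in the repair an analyst might make unprompted: keep the message date where there is one, and use the flag date in control. The control clock would then include the wait for an appointment and the reminder clock would not. Appointments are also when situations get resolved, so the reminder clock would start at an opportunity to resolve. That favours reminders without any effect.

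**Working it through.** The article gives no figure for the time outcome (its sample size concerns the proportion resolved), so there is no stated result to reproduce. The check has three parts.

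**1. Does the origin exist in each arm?**

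| | Reminder arms | Control |
|---|---|---|
| Message shown for the patient | Yes, tied to an appointment | No |
| Stated time zero | Date of first message | None |
| Algorithm flag date | Derivable | Derivable, but not named as origin |

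**2. What happens if the two dates are mixed?**

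The article gives neither visit rates nor the chance of resolution per visit, so both are assumptions. The model is:
- all situations are flagged at month 0, and follow-up is 12 months (the trial's length);
- visits are random at v per year (v = 2, 4, 6, 12);
- the message is displayed at the first visit;
- resolution happens only at visits, with probability q each (q = 0.05 to 0.30), the same in both arms.

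With t in months, the share resolved by t is:
- flag clock: 1 − exp(−v·q·t/12);
- message clock: 1 − (1 − q)·exp(−v·q·t/12), because a share q resolves at the visit that starts the clock.

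For v = 4, q = 0.2, t = 6, the exponent is 4 × 0.2 × 6/12 = 0.4:
- flag clock (control): 1 − exp(−0.4) = 33.0%;
- message clock (reminder): 1 − 0.8 × exp(−0.4) = 46.4%.

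The true effect is nil. A simulation of 200,000 situations per arm gives the same two percentages. Its hazard ratios (Mantel–Haenszel over monthly intervals) are:

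| Visits per year | Hazard ratio, mixed clocks, q = 0.05 to 0.30 |
|---|---|
| 2 | 1.61 to 1.89 |
| 4 | 1.26 to 1.48 |
| 6 | 1.15 to 1.36 |
| 12 | 1.10 to 1.25 |

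With the flag clock in both arms the hazard ratio is 0.99 to 1.02 throughout.

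The mean wait left out of the reminder clock is 12/v months: 6 at v = 2, 3 at v = 4, 1 at v = 12. At v = 2 some waits exceed the trial. Among situations displayed within 12 months the mean is 6 − 12·exp(−2)/(1 − exp(−2)) = 4.1 months.

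**3. Is the proportion resolved affected?**

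Only if situations never displayed are dropped from the reminder arms. Under the same model the never-displayed share is x = exp(−v): 13.5% at v = 2, 1.8% at v = 4, near 0 at v = 12. If r is the share resolved among those displayed, the share in the full set is r(1 − x), and the spurious gain is r·x. Putting r at the article's assumed 59%:
- v = 2: 0.59 × 13.5% = 8.0 points;
- v = 4: 0.59 × 1.8% = 1.1 points.

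In the simulation, v = 2 and q = 0.3 gave 45% in the full set against 52% among displayed situations only.

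**The case against.** The fair reply is that the article leaves the control clock undefined; it does not set two different clocks. Several passages point towards an arm-neutral approach. The weekly identification of improvable patients carries no arm restriction, Table 3 lists whether a reminder was generated separately from whether the situation can be improved, and the time analysis is headed by the situation rather than the message. If the authors meant the date on which the algorithm generates a reminder, silently in control, then clock and risk set would match. This stands as a reason not to call the bias demonstrated. It does not rescue the definition, because none of these passages names the origin and the two that do both name the message.

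A reader might go further and infer the following, which the text does not support:

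- **That the reminder clock starts at an attended visit.** The pop-up depends on opening the record from the appointment list, and in two arms the icon shows before any record is opened. Display depends on an appointment, not on attendance. Missed appointments would make the bias smaller than in the model above.
- **That any control date must come earlier.** Primary care visits are collected, so the first visit after the flag could serve as a control origin. It would be neither systematically earlier nor include non-attenders.
- **That reminders are selected after randomisation.** The Intervention section says "There is also an option to ignore or exclude a recommendation for a particular patient", but no passage removes excluded or undisplayed reminders from the analysis, and Table 2 defines resolution without reference to them.

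The primary objective and sample size also rest on resolution, not on time. That limits the reach of the point, but the Outcomes section still places time within the main outcome.

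**Conclusion.** The point holds for the time component. Its stated origin cannot occur in control, no control origin is given, and between-arm survival comparisons are planned on it. That conclusion rests on the text alone.

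The size is conditional. It assumes that the message date is kept in the reminder arms and an earlier date such as the flag is used in control. Under the simple visit model this gives null hazard ratios of about 1.1 to 1.9 over 12 down to 2 visits a year, always favouring reminders. Visit rates and resolution probabilities are assumptions, so these figures are illustrations and not estimates for this trial.

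For the proportion resolved, no defect is shown. A reader might infer a spurious difference as large as the 10-point target, for instance 0.59 × 20% = 11.8 points if a fifth of situations were never displayed. Under the model that needs about 1.6 visits a year, since −ln(0.20) = 1.6, and a denominator of displayed reminders only, which the article does not state. Within 2 to 12 visits a year, at a 59% resolution rate, the most it could reach is about 8 points, and about 1 point at 4 visits.

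**What to change.** Change the definition in the abstract and in Outcomes, and carry it into the time analysis:

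- In all four arms, time zero is the date on which the weekly SISAP algorithm first flags the situation as improvable, or trial start if the situation is already present then. Run the algorithm silently in control centres and store the date.
- Analyse the same flagged set in every arm, whether or not a reminder was displayed or was excluded by the professional.
- Report time from first display only as description, within the reminder arms.

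The cost is wording, plus running an existing algorithm on control records and keeping its dates. The downside is that the effect is diluted by patients for whom no reminder is ever displayed. That is still the effect of offering reminders as a policy, which is the comparison that the randomisation supports.

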### Data collection and management

The ICS primary care information system (SISAP) will be used to identify patients with a health status that could be improved by the health reminders, and execute a weekly update of patient status. The variables required to execute these algorithms will be obtained from the clinical registry of electronic health records. They include patient diagnoses (by CIE-10 code), primary care visits, clinical variables, drug prescriptions, and vaccinations. In addition to the variables specific to the intervention (resolution of the reminder), other explanatory and descriptive variables will be collected (Table 3). Data for the EQR (quality of data recording) will be collected from the SIDIAP database (*Sistema d’Informació per al Desenvolupament de la Investigació en Atenció Primària*) (Bolíbar et al. 2012). Moreover, the Medea socioeconomic index (Domínguez-Berjón et al. 2008). The EQA, EQPF (prescription quality standard), and other variables at the level of the professional or PCC will be obtained from the ICS information system.

**Table 3 Tab3:** Variables included in multi-level analysis

Variable	Explanation
Variables at the reminder level	
Type of clinical activity required^a^	Preventive or follow-up activities, immunizations, treatment initiation
Reminder generated	Yes or no
Clinical situation can be improved	Described in Table 1
Age and sex^a^	Older populations generate a higher number of clinical situations that can be improved because of the relationship between age and morbidities
Comorbidity, weighted according to CRG^a^	CRG (Clinical related groups) classify patients according to morbidity, based on diagnoses, status and severity in different categories. Each category has a morbidity weight. A priori, greater morbidity should generate a greater number of improvable clinical situations
Variables at the professional/PCC level	
Socioeconomic level of the PCC	Medea Index
Rurality	Construct based on size of municipality and population/Km^2^
Teaches family medicine	PCC or team member is accredited for postbaccalaureate training in Family and Community Medicine
Teaches basic nursing	PCC or team member is accredited for baccalaureate training in Nursing
Percentage of assigned population visiting the PCC previous year	Percentage of the assigned population who visited the PCC/individual health professional during the year prior to the study. A priori, professionals who see a larger percentage of their assigned patients have more opportunities for interventions to improve clinical situations.
Frequency of patient visits	Number of visits per year/population with at least one visit in the previous year. A priori, a greater number of patient contacts with a health professional will yield more opportunities to correct clinical situations.
EQA	Synthetic clinical indicator consisting of a group of indicators based on scientific evidence.
EQPF	Synthetic indicator developed by the ICS Department of Medication Strategy, including 21 indicators related to the quality of the prescription
EQR	Synthetic indicator that analyses the difference between population prevalence and a patient cohort, which identifies professionals with a good level of recording quality

*EQA* quality care indicator, *EQPF* prescription quality indicator, *EQR* quality of data recording, *CRG* clinical related groups, *PCC* primary care centre

^a^Anonymized data from patient records

### Sample size

A 10 % difference between the proportion of resolved reminders and the assumed proportion in the intervention group of 59 % will be considered clinically relevant (Demakis et al. 2000). Assuming an alpha error of 0.01, 95 % power, and 10 % loss to follow-up, and correcting for an intraclass correlation in the PCCs of 0.05, each of the 4 study groups will require 15,950 reminders, a total of 63,800. The estimated number of reminders to be generated is shown in Table 1. Nonetheless, due to the design of the computerized tool, the need for cluster randomization, and the availability of the universal sample, it is not considered necessary to limit the study to the calculated sample size.

